# Pancreatoduodenectomy versus total pancreatectomy and simultaneous intraportal islet autotransplantation for periampullary cancer at high-risk of postoperative pancreatic fistula (XANDTX-trial): Protocol of a randomized controlled pilot trial

**DOI:** 10.1371/journal.pone.0327949

**Published:** 2025-07-28

## Abstract

**Introduction:**

Pancreatic surgery remains associated with significant morbidity. Pancreatoduodenectomy (PD) with high-risk stigmata for postoperative pancreatic fistula (POPF) may delay or hinder administration of adjuvant therapy. Total pancreatectomy (TP) prevents POPF-associated complications but implies permanent exocrine and endocrine insufficiency. Islet autotransplantation (IAT) has the potential to compensate endocrine function.

**Methods and analysis:**

XANDTX is a single-centre randomized controlled pilot trial comparing high-risk PD with TP and simultaneous IAT in patients with periampullary cancer. After screening for eligibility and obtaining informed consent, a total of 32 adult patients will be intraoperatively randomized in a 1:1 ratio. The primary hypothesis is that TP with IAT prevents POPF-associated complications and leads to a shorter period to initiation of adjuvant therapy and a higher overall rate of adjuvant therapy administration.

Secondary endpoints include perioperative morbidity and mortality, metabolic outcome, quality of life (QoL) and oncological long-term outcome. Each patient will be followed up for 5 years.

**Discussion:**

The XANDTX pilot trial will aim to provide surgical and oncological feasibility and safety data of total pancreatectomy with simultaneous islet autotransplantation in management of resectable periampullary cancer. The results will form the basis for a further confirmatory controlled study.

**Trial registration:**

This study was registered on ClinicalTrials.gov (NCT05843877) on February 27, 2023 and EudraCT (2023-507773-17-00) on April 18, 2024.

## Introduction

Despite steady improvement in surgical technique, optimization of perioperative management and increasing centralization, pancreatic surgery remains associated with significant morbidity. Although mortality could be significantly reduced, morbidity is still reported at a rate of 40–60%, even in high-volume centers [1]. Especially for pancreatic malignancies, tumor resection represents the only potentially curative therapeutic procedure. One of the most common and potentially life-threatening complications in pancreatic surgery is postoperative pancreatic fistula (POPF), occurring at varying frequency depending on the type and extent of pancreatic resection or intervention. Pancreatic anastomosis in pancreaticoduodenectomy (PD) represents an “Achilles heel” in pancreatic surgery as leakage or insufficiency of the pancreaticoenteric anastomosis can result in POPF and POPF-associated complications. Over the last decades, many studies have analyzed POPF risk factors, with the strongest evidence for a considerably increased prevalence of POPF in patients with soft pancreatic parenchyma and a small pancreatic duct diameter [2–4].

Since total pancreatectomy (TP) avoids a pancreaticoenteric anastomosis and therefore circumvents POPF-associated complications, TP has recently become a major topic of scientific discussion in the surgical community as a potential alternative to partial pancreatic resection in patients with a high-risk constellation. In the treatment of patients with periampullary cancers, primary TP provides surgical and oncological outcomes similar to standard pancreatic head resection [5]. Recently published studies compared the surgical outcomes of high-risk PD and TP, often favouring TP [6–8]. A retrospective analysis also reported on generally comparable nonspecific, cancer-specific, and pancreas-specific quality of life (QoL) between TP and high-risk PD [9]. However, the psychosocial impact of complete insulin-deficient and often brittle diabetes in combination with severe exocrine insufficiency were significantly pronounced after TP, emphasising the life-long burden related to a complete removal of pancreatic parenchyma. Intraportal islet autotransplantation (IAT) simultaneous to TP is a potential option to prevent or alleviate pancreoprivic diabetes through partial preservation of endogenous insulin secretion [10–12]. Specifically, pancreatic islets are enzymatically isolated from the non-tumor-bearing part of the pancreas after TP and are re-infused via the portal vein, resulting in intrahepatic engraftment [13,14]. IAT thereby has a significant positive effect on metabolic control and QoL [15–18].

The objective of the XANDTX trial is to obtain data on the treatment effect and safety of combined TP and simultaneous IAT in patients with periampullary carcinoma at high-risk for POPF. The feasibility and safety data regard both surgical and oncological outcome comparing to the current surgical standard procedure.

## Methods and analysis

### Trial design and timeline

XANDTX is conceptualized as a single-centre open-label, randomized, controlled therapeutic exploratory feasibility study. Patients planned for elective periampullary tumor resection will be assessed for eligibility and eligible patients will be informed about the trial in detail. After written informed consent and in the case of intraoperative presence of a POPF high-risk constellation (soft pancreatic texture and pancreatic duct diameter ≤ 3 mm), 32 patients will be intraoperatively allocated in a 1:1 ratio to undergo either PD or TP with simultaneous IAT (Fig 1). Randomization will be performed via sealed envelopes (block randomization).

**Fig 1 pone.0327949.g001:**
[figure not shown]
Study flowchart.

The recruitment start for this study was in January 2025. The planned recruitment period is 24 months. The individual follow-up time after surgery is 60 months, resulting in a study duration of 84 months, after which results are expected. The trial will be reported according to the Consolidated Standards of Reporting Trials (CONSORT) Extension for Randomized Pilot and Feasibility Trials [19].

### Population and eligibility criteria

In this study, 32 patients with periampullary carcinoma and high-risk profile for the occurrence of POPF will be treated. Inclusion of minors and non-consenting subjects is not intended. All in- and exclusion criteria are listed in Table 1. A balanced gender distribution in the study population is aspired. However, the determination of possible sex-specific differences in efficacy or safety of the treatment arms will likely be impossible due to the small case number and must be investigated in larger follow-up studies. The Department of Visceral, Thoracic and Vascular Surgery at the University Hospital Carl Gustav Carus Dresden has a focus on oncological pancreato-biliary surgery, performing about 150 pancreatic resections (including at least 70 PDs) annually. Approximately 20 of 70 cases of pancreatic head resections meet the criteria of a high-risk profile for POPF. Therefore, recruitment of 16 patients/year appears feasible, resulting in a planned recruitment duration of 24 months.

**Table 1 pone.0327949.t001:** Inclusion and exclusion criteria.

Inclusion criteria	Exclusion criteria
• suspected or histologically confirmed periampullary carcinoma/tumor and indication for PPPD or Whipple surgery • high-risk constellation for the development of POPF: soft pancreas and pancreatic duct diameter ≤ 3 mm • male and female patients aged 18 years and older • written informed consent	• patients who are undergoing simultaneous surgery in addition to PPPD or Whipple surgery • expected lack of adherence • histologically confirmed other primary tumor • previous transplantation of an organ or tissue • known infection with HIV (HIV antibodies) • positive hepatitis C antibodies, positive hepatitis B surface antigens and hepatitis Bc antibodies • insulin-deficient diabetes mellitus • pregnant or breastfeeding women • participation of the patient in another clinical trial according to AMG within the last 4 weeks before inclusion

Abbrevations: AMG, Arzneimittelgesetz (German Medicinal Products Act); HIV, human immunodeficiency virus; PD, pancreaticoduodenectomy; POPF, postoperative pancreatic fistula.

### Ethics dissemination

The present trial will be conducted in accordance with the Declaration of Helsinki, the international principles of GCP (ICH-GCP E6 guidelines), the provisions of the AMG and the GCP Regulation (2004) and all other applicable laws including data protection laws and the European General Data Protection Regulation. The study protocol (version 6.0F, March 27, 2024) was reviewed and approved by the responsible federal authority (Paul-Ehrlich-Institut (Agency of the German Federal Ministry of Health)) and the responsible ethics committee through the EU portal in accordance with the Regulation (EU) 536/2014 (EUCT-number: 2023-507773-17-00).

Each included patient will be informed about the clinical trial prior to enrollment in detail by investigators. A detailed conversation between a medical member of the trial team and the patient will take place discussing all information. These information will be shared in oral as well as in written form. Potential participants will only be asked to sign and personally date two copies of the consent form upon clarification of all questions. Subsequently, one copy of the patient information/consent form will be handed to the participating individual; the second copy will remain at the study site.

### Description of the investigational product

The investigational medicinal product consists of isolated and purified autologous pancreatic islets and will be manufactured, tested and released patient-related under GMP conditions according to the German Drug and Drug Substance Manufacturing Regulation (Arzneimittel- und Wirkstoffherstellungsverordnung, §16) under the responsibility of the University Hospital Carl Gustav Carus at the Technical University of Dresden.

The pancreatic islets are isolated and purified from the patient’s own pancreatic tissue according to §13 Medicines Act (AMG). The pancreatic resection is performed in accordance with §20b AMG. The isolation process takes place after preparation of the tissue (liberation of surrounding fatty/binding tissue) by distension with an enzyme mixture (collagenase, neutral protease, DNAse) via the pancreatic duct and initiation of the enzymatic digestion process by heating to 35°C and mechanical support. After release of the intact islet cell clusters from the surrounding tissue, the digestion process is stopped by cooling the system and adding albumin-containing medium. Subsequently, the tissue suspension is washed several times, and separation of islet cell clusters and exocrine tissue components is achieved by density gradient centrifugation. The purified islet preparation is transferred to transplantation medium after repeated washing steps. The process is accompanied by defined in-process controls. 

### Treatment regimen

In the control arm, oncological PD is performed as pylorus-preserving pancreatic head resection (PPPD) or as classic Whipple procedure with the only requirement for the form of reconstruction being that the pancreatic reconstruction must be to the jejunum. In the intervention arm, oncological total pancreatectomy is performed. This procedure may or may not include simultaneous splenectomy/partial gastric resection, depending on the situs. In the case of total pancreatectomy, application of the investigational drug then follows once after the above-mentioned islet cell isolation and purification steps. Multiple or re-transplantation is not intended in the context of this study. The extension of the surgical procedure (e.g., oncological reasons) is explicitly not limited by the study protocol.

IAT is performed under general anesthesia at the end of the pancreatic resection. For this, portal vein is accessed and punctured with a three-lumen central venous catheter (CVC). The CVC is advanced into the right portal vein branch. The correct position is checked and documented intraoperatively using ultrasound. A continuous pressure system is connected to the CVC to measure portal vein pressure. After establishing the appropriate infusion systems, the preparation is infused by gravity over a period of approximately 30 minutes. The portal vein pressure is continuously monitored. In case of a pressure increase of >50%, the infusion is slowed down or paused and continued after normalization of portal vein pressure. In case of an irreversible pressure increase above 100%, the infusion is stopped and the remaining preparation is withdrawn.

All study patients receive standard postoperative interdisciplinary follow-up in the surgical intensive care unit to guarantee specific monitoring of islet function and adjustment of diabetes treatment, if applicable.

### Outcome

The primary endpoint of this study is defined as the time between the day of surgery and the day on which a oncologist decides that the patient is fit to receive adjuvant therapy.

The following points were defined as secondary outcome parameters:

perioperative morbidity and mortalitypreoperative and postoperative quality of lifemetabolic outcomefrequency and type of adverse eventslong-term oncologic outcome including time between surgery and actual start of chemotherapy

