#### Statistical methods.

The data collected within this exploratory trial will provide the basis for a subsequent confirmatory controlled study. Therefore, no formal sample size estimation was performed. Assuming an event rate of about 60 percent, a sample size of 30 patients (15 individuals per treatment group) allows for the detection of a hazard ratio of approximately 0.31 (two-sided significance level of 10%, power of 80%). Assuming a drop-out rate of 5%, 16 patients per treatment group will be included. 

The main analysis will be performed after completion of the two-year follow-up period (including data collection and cleaning) in the entire intention-to-treat population. No interim efficacy analyses are planned in this study. All analyses will be performed using SAS 9.4 or higher.

The confirmatory analysis of the primary endpoint and the analysis of the secondary endpoints will be performed according to ICH E9 [21] using the full analysis set (intention-to-treat population) and follow the intention-to-treat principle. The full analysis set will include all randomized patients.

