##### Safety analysis set

The safety analysis set includes all patients in whom the investigational therapy was used.

For long-term oncologic outcomes (survival analyses), patients lost to follow-up and patients deceased within the observation period will be censored. A per-protocol analysis is planned for sensitivity analysis.

The primary endpoint (time between surgery and day of “fit for adjuvant treatment”) is defined as the interval between day of surgery and day of oncologists decision that patient is fit to start the administration of adjuvant chemotherapy, measured in days. It will be analyzed using Kaplan-Meier estimators (with a two-sided confidence level of 90 percent). Comparison of the primary endpoint between the treatment groups will be performed using the log-rank test. In case of proportional observed hazards in the control and treatment groups, a Cox proportional-hazards model will be used to examine which covariates have an impact on the hazard ratio of the two treatments. Safety analysis will include the frequency of (serious) adverse events in the safety analysis set. Annual safety analyses will be performed in accordance with regulatory requirements. Frequencies and types of adverse events (AE, SAE) will be summarized as relative frequencies (proportions) and, if applicable, the occurrence of specific events (at the patient level) of the two groups will be compared using chi-square test. QLQ-C30/Pan26 questionnaires will be analyzed using a mixed model with the patient as a random factor analysis, including comparison of changes in quality of life over time between the two treatment groups, and respective covariates potentially impacting quality of life within each of the two treatments. Exact Chi-Square test will be used to analyze perioperative morbidity and mortality. Metabolic outcome over time will be analyzed using a mixed model with the patient as a random factor. To analyze the oncologic outcome, a Cox regression model will be used.

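### The primary hypothesis is about starting and receiving adjuvant therapy, but the primary endpoint is the day a patient is judged fit for it, so the primary test does not address the hypothesis as stated

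*Protocol article*

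**What the plan says.** The abstract (Methods and analysis) gives the primary hypothesis in three parts: fewer fistula-associated complications, and a treatment that "leads to a shorter period to initiation of adjuvant therapy and a higher overall rate of adjuvant therapy administration".

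The Outcome section defines the primary endpoint as the time from surgery to "the day on which a oncologist decides that the patient is fit to receive adjuvant therapy". The analysis text under Safety analysis set repeats this, ending the interval at the "day of oncologists decision that patient is fit to start the administration of adjuvant chemotherapy, measured in days". It assigns Kaplan-Meier estimation and a log-rank test.

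The Outcome section lists "time between surgery and actual start of chemotherapy" as part of long-term oncologic outcome, among the secondary parameters. The proportion of patients who receive adjuvant therapy is not listed.

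Trial design and timeline calls the trial a "single-centre open-label, randomized, controlled therapeutic exploratory feasibility study". Statistical methods says that "The data collected within this exploratory trial will provide the basis for a subsequent confirmatory controlled study", yet also refers to "The confirmatory analysis of the primary endpoint and the analysis of the secondary endpoints".

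**The concern.** Being declared fit, starting treatment and ever receiving treatment are three different events. The article separates the first two itself by listing them as different outcomes. The hypothesis concerns the second and third, while the primary test concerns the first.

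A positive log-rank result would therefore show that patients in one arm were judged fit sooner. It would not by itself show that they started sooner or that more of them were treated. The rationale in the Discussion rests on receipt: about one third of patients receiving indicated adjuvant treatment, and 67.4% of those with serious fistula-associated complications never receiving chemotherapy. A fitness date cannot be compared with either figure.

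The event is also a judgement, and the trial is open-label, so the endpoint is in principle more exposed to knowledge of the arm than a recorded date of first administration. Because the results are meant to shape a later confirmatory trial, a mismatch left here may be carried forward.

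**Working it through.** **Hypothesis against outcomes**

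| Part of the primary hypothesis (abstract) | Where it is measured | Rank |
|---|---|---|
| Fewer fistula-associated complications | Perioperative morbidity | Secondary |
| Shorter time to initiation | Time to actual start of chemotherapy, within long-term oncologic outcome | Secondary |
| Higher rate of administration | No named outcome | None |
| (not in the hypothesis) | Time to being judged fit | Primary |

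No part of the hypothesis is measured by the primary endpoint.

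**The plan's own figures**

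Inputs from Statistical methods: 30 patients (15 per group), event rate about 60%, two-sided 10% level, power 80%, drop-out 5%. The article does not name the event behind the 60%.

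- Events: 30 × 0.60 = 18.
- Detectable hazard ratio (Schoenfeld, 1:1): exp(−2 × (1.645 + 0.842)/√18) = exp(−1.172) = 0.310. The stated value of about 0.31 reproduces.
- Power at 0.31: Φ(|ln 0.31| × √18/2 − 1.645) = Φ(2.484 − 1.645) = 0.799.
- Drop-out: 15/0.95 = 15.8, so 16 per group, as stated.

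The formula depends only on the size of the log hazard ratio, so 0.31 and its reciprocal 3.23 give the same result. No stated figure is wrong.

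**Cost of moving the event to actual start**

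If the 60% refers to being judged fit, and nobody starts without that judgement, the start rate can be at most 60%. The article gives no expected start rate, so the rates below are assumptions. One third is the low end because the Discussion cites it for pancreatic surgery in general.

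Events d = 30 × rate; detectable hazard ratio = exp(−2 × 2.487/√d); power = Φ(1.171 × √d/2 − 1.645).

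| Assumed start rate | Events | Detectable hazard ratio | Power at 0.31 |
|---|---|---|---|
| 60% | 18 | 0.31 | 80% |
| 50% | 15 | 0.28 | 73% |
| 40% | 12 | 0.24 | 65% |
| One third | 10 | 0.21 | 58% |

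The formula requires 19 events at 0.31 after rounding up. At a start rate of one third, that means 19 × 3 = 57 evaluable patients, against 30 planned.

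**The case against.** The best defence is that fitness is a reasonable choice of endpoint. Eligibility extends to suspected carcinoma, so actual start may depend on final histology and indication as well as on patient choice and logistics. Fitness lies closer to surgical recovery, which the intervention is meant to improve. This stands as an argument for keeping the endpoint. It does not defend a hypothesis that names something else.

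A second defence is that the trial is a pilot, which limits the consequence. That also stands in part, although the article uses the word confirmatory for the primary analysis and intends the data to inform the next trial.

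A reader might infer three stronger points, which the document does not support.

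- **That the trial cannot support its claim at all, or has no objective outcome beside the judgement.** Time to actual start is a named secondary outcome and gives direct evidence on initiation. It plausibly falls under the Cox model that the article assigns to oncologic outcome, so it cannot be called unanalysed either.
- **That the deciding oncologist is known to be unblinded, with no fitness criteria or common assessment times.** The article says only that the trial is open-label. Assessor, criteria and timing may be set in the full protocol or the visit schedule (S1 Table), neither of which is shown.
- **That the size of any assessment bias can be stated.** The article gives neither expected proportions per arm nor the timing of fitness decisions from which to derive it.

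**Conclusion.** The mismatch is real and can be read directly from the text. The primary log-rank test does not address initiation or administration; initiation is covered only at secondary level, and the administration rate is not a named outcome. The trial can still inform the question of initiation, but not through its primary result.

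The exposure to bias of a judged endpoint in an open-label trial is a general weakness and not a demonstrated defect here. The case does not depend on it.

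The effect is on what may be concluded; the sample-size figures are unaffected. The power range of 58% to 80% for actual start assumes 30 evaluable patients, a hazard ratio of 0.31, the Schoenfeld approximation and the assumed start rates. It argues against making actual start the primary or a co-primary endpoint at this size. The point should be settled before analysis.

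**What to change.** 1. Reword the primary hypothesis as a difference in time to being declared fit for adjuvant therapy, so that it matches the endpoint in the Outcome section and the analysis text.
2. Name time from surgery to actual first administration of adjuvant therapy as the first key secondary outcome, together with the proportion of randomised patients who ever start. Take it out of the general item on long-term oncologic outcome.
3. Analyse it by the same Kaplan-Meier and log-rank method as the primary endpoint, in the full analysis set, with the same 90% confidence level.
4. State that any claim of earlier or more frequent adjuvant therapy will rest on this outcome and not on the fitness endpoint.

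The cost is protocol and analysis-plan wording. Time to start is already a listed outcome, and the proportion starting follows from the same records. As a key secondary outcome it leaves the planned 32 patients unchanged. The drawback is that actual start also reflects indication, patient choice and logistics, and may yield fewer events than fitness does. It should therefore stand beside the fitness endpoint, with its result read mainly as an estimate for planning the next trial.
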